## 8.9 Follow-up of serious adverse events

All serious adverse events must be documented and followed up until the event either resolved, subsided, stabilized, disappeared or is otherwise explained or the study subject is lost to follow-up, but not longer than 6 after the last vaccination. All follow-up activities have to be reported, if necessary on one or more consecutive SAE report forms in a timely manner. All fields with additional or changed information must be completed and the report form should be forwarded to the Study Contact for Reporting Serious Adverse Events as soon as possible but latest within 5 calendar days after receipt of the new information.

Clinically significant laboratory abnormalities will be followed up until they have returned to normal, or a satisfactory explanation has been provided. Reports relative to the subsequent course of an adverse event noted for any subject must be submitted to the Sponsor.

## 8.10 Pregnancy

Subjects who become pregnant during the study period (up to and including one month [minimum 30 days] after receiving the last vaccine dose) must not receive additional doses of vaccine but may continue other study procedures at the discretion of the investigator.

Subjects should be instructed to notify the investigator if it is determined after completion of the study that they became pregnant either during the study or within one month (minimum 30 days) after receiving the last vaccine dose.

A pregnancy should be followed to term, any premature terminations reported, and the health status of the mother and child including date of delivery and the child's gender and weight should be reported to Pevion Biotech Ltd. after delivery.

## 8.11 Treatment of adverse events

Treatment of any adverse event is at the sole discretion of the investigator and according to current Good Medical Practice. The applied measures should be recorded in the CRF of the subject.

## 9 Study Completion and Discontinuation

### 9.1 Definitions

Discontinuation from the study can occur under the following circumstances:

**Screening errors:**

From an analysis perspective, a 'screening error' is any subject who was enrolled into the study, i.e. was attributed a CRF with subject number, but was withdrawn (before or after randomization) prior to vaccination for reasons such as protocol violation (inclusion/exclusion criteria), 'force majeure' or withdrawal of consent.

**Lost to follow-up:**

From an analysis perspective, a 'lost to follow-up' is any subject who completed all protocol specific procedures up and including to Day 1, including vaccination, but was then lost to any further follow-up, (no safety information and no efficacy endpoint data ever became available)

**Drop-outs:**

Any subject for whom data is available for at least one follow-up visit but did not complete the study as foreseen in the protocol.

### 9.2 Reasons for drop-out

It should be specified on the End of Study page of the CRF, which of the following possible reasons were responsible for drop-out of the subject from the study:

- Adverse events
- Protocol violation (specify)
- Consent withdrawal, not due to an adverse event ,
- Migrated/moved from the study area
- Other (specify)

### 9.3 Procedures for handling subjects discontinued

Investigators should make an attempt to contact those subjects who do not return for scheduled visits or follow-up. Information gathered should be described on the Study Conclusion page of the CRF and on Medication/Adverse event forms.

### 9.4 Data and Safety Monitoring Board

A Data and Safety Monitoring Board (DSMB) will be established if one of the following situations occurs:

- One or more subjects experienced a serious adverse reaction assessed as related to the vaccine by the investigator
- One or more subjects experienced anaphylaxis
- Two or more subjects in a single dose and antigen cohort experienced a severe adverse event not explained by a diagnosis unrelated to vaccination. (For grading of severity see Appendix 4)

The DSMB will then analyze the data and decide on the continuation of the study.

## 10 Data evaluation

### 10.1 Data handling

The data collected with the CRFs will be entered into a database set up by Hesperion Ltd, Allschwil. Hesperion is responsible for data handling and record keeping.

The statistical analysis of the data and the preparation of tables and listings for interim and final reports will be performed by the project statistician, [name], Swiss Tropical Institute.

### 10.2 Primary tests

#### Safety and Tolerability

- Occurrence of local and systemic adverse events
- Occurrence of clinically significant hematological and biochemical abnormalities

#### Immunogenicity

- ELISA for antibody titers against PEV 301 and PEV 302, performed by Pevion Biotech Ltd.
- Western Blotting and IFA for antibody titers crossreactive with *P. falciparum* parasites (blood stages and sporozoites, respectively), performed by STI

### 10.3 Secondary tests

- T-cell proliferation assays, performed at STI
- Parasite growth/invasion inhibition assays, performed at STI
- IgG isotyping, performed at STI
- ELISPOT and clonal T-cell analyses, performed at STI
- Influenza ELISA/HIT, performed at Pevion Biotech Ltd.

### 10.4 Statistical hypothesis

PEV 301 and PEV 302 are safe for inoculation into non-immune subjects. No serious adverse events attributable to either vaccine occur in the study population. One or both of the vaccines induce specific immune responses in at least 1/3 of the volunteers.

### 10.5 Sample size calculation

The sample size of this pilot study is determined by the requirement to determine safety of each formulation and dose. A sample size of 8 in each group constitute a reasonable sample size to estimate the frequency of AEs with an acceptable accuracy, allowing for dropouts. The study is not powered to ensure that differences in safety or immunogenicity between regimens will be statistically significant.

### 10.6 Statistical analysis

Demographic data of each study group will be tabulated.

#### Safety data:

Listings will be made of the safety data collected at each time point.

Descriptive statistics will be used to analyze adverse events (AEs) including intercurrent illnesses. The number of AEs and their severity will be reported using frequency tables. With frequently occurring (10 or more) event types, effects of dose and vaccine will be tested by

recording the presence/absence of the event in each patient and using logistic regression models to test for differences between groups.

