| STATISTICAL METHODS AND EVALUATION OF DATA | 
Demographic data of each study group will be tabulated.
 
Safety data: Listings will be made of the safety data collected at each time point. Descriptive statistics will be used to analyze adverse events (AEs) including intercurrent illnesses. The numbers of AEs and their severity will be reported using frequency tables. With frequently occurring (10 or more) event types, effects of dose and vaccine will be tested by recording the presence/absence of the event in each patient and using logistic regression models to test for differences between groups.
 
Immunogenicity data: Immunological data for each time point will be analyzed separately.
 
 
Descriptive statistics (minimum, maximum, median, geometric mean, arithmetic mean and quartiles) will be computed for each immunological measure and each time point, separately for each group.
 
For each volunteer, the ratio of the immunological measure to that assessed at baseline (during screening) will be computed. Descriptive statistics of these ratios (minimum, maximum, median, geometric mean, and quartiles) will be computed for each immunological measure and each time point, separately for each group.
 
Wilcoxon test will be used to compare the immunological measures between doses and between group E and groups C or D (as appropriate) for each immunological measure, each time point and each antigen.
 
                                                                                                                                                                                                                                                                                                                                                                                                                                                                                                                                                                                                                                                                                                                                                                                                                                                                                                                                                                                                                                                                                                                                                                                                                                                                                                                                                                                                                                                                                                                                                                              |                     |                                                                                                                                                          |                 |                                          |

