## 3 Study Design

This prospective phase I, single centre, randomized, single blind, placebo controlled, dose escalating study will be conducted in 46 healthy adult volunteers. Eligible study participants will be randomized into six groups: PEV 301 10 µg (group A, n = 8) or PEV 302 10 µg (group B, n = 8) or PEV 301 50 µg (group C, n = 8) or PEV 302 50 µg (group D n = 8) or PEV 301 50 µg plus PEV 302 50 µg (group E, n = 8) or virosomes alone (group F, n = 6).

Study participants will be vaccinated three times, i.e. at days 1, 64(+2) and 183(+2) and followed-up 3 times after each vaccination. If any of the study groups does not show any immune response 3 weeks after the 2nd vaccination, no 3rd vaccination will be given to that group, i.e. the study for that group will be terminated 3 weeks after the 2nd vaccination.

Groups C & D (PEV 301 50 µg; PEV 302 50 µg) will be started 5 weeks after the 1st vaccination of groups A, B.

Group E (PEV 301 plus PEV 302) will be started 5 weeks after the 2nd vaccination of groups C and D.

Group F will be distributed and serve as a control in all groups receiving the active product.

The total duration of the study for each participant is 31 weeks, the number of visits is 13.

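### The '10 or more' gate on adverse event tests has no stated unit and exceeds every group size, so it can withhold the planned test from a reaction confined to one group

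*Protocol*

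**What the plan says.** Section 10.6 of the protocol, under Safety data, first gives a descriptive analysis: "The number of AEs and their severity will be reported using frequency tables". It then adds formal testing for a subset of events. The opening of that sentence sets the gate: "With frequently occurring (10 or more) event types, effects of dose and vaccine will be tested by". Its remainder sets the method, which codes each volunteer as affected or not and fits a regression: "recording the presence/absence of the event in each patient and using logistic regression models to test for differences between groups". The Synopsis carries the same rule. Neither place says what the 10 counts.

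Section 3 gives the group sizes. Groups A to E have 8 volunteers each, and the control group is "virosomes alone (group F, n = 6"). Section 10.5 rests the sample size on estimating adverse event frequency within each group: "A sample size of 8 in each group constitute a reasonable sample size to estimate the frequency of AEs". The same section says that the study is not powered to show differences between regimens.

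Section 3 plans three vaccinations per volunteer. Section 8.2 records adverse events for at least 30 days after each dose. Section 8.3.1 opens a new record when an event changes significantly in frequency or intensity.

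**The concern.** The gate and the test use different quantities. The test asks whether each volunteer had the event. The gate asks for 10 of something unstated, in a trial where no group has 10 members.

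Safety and tolerability are the primary objective, and this is the first study of these two products in humans. A reaction tied to one formulation or dose is the pattern that a test of dose and vaccine effects should pick up. A gate above the group size works against that pattern, while an event spread thinly over all groups passes more easily. The report could then carry p-values for diffuse events and none for a complete separation between one vaccine group and the rest.

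**Working it through.** **Inputs.** Five groups of 8 and one of 6 (Section 3); gate of 10, unit unstated (Section 10.6); three doses, or two if a group stops after the interim analysis (Sections 3 and 10.8). The total reproduces: 5 × 8 + 6 = 46, as Section 3 states. The protocol gives no derivation of the 10 and no significance level; two-sided 0.05 is assumed below.

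**Most that one group can contribute to the gate**

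- Counting volunteers: 8 in a vaccine group, 6 in group F. Both are below 10, so an event confined to one group cannot qualify.
- Counting occurrences, one record per dose: 8 × 3 = 24 over three doses, 8 × 2 = 16 over two. Reaching 10 needs 10/8 = 1.25 occurrences per volunteer. A reaction seen once in each of 8 volunteers gives 8 and does not qualify. Three volunteers reacting at all three doses plus a fourth reacting once gives 3 × 3 + 1 = 10 and does qualify, with half as many people affected.

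**What an ungated exact test would show** (two-sided Fisher, vaccine group v none affected)

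| Affected | v 0/8 | v 0/6 |
|---|---|---|
| 4/8 | 0.077 | 0.085 |
| 5/8 | 0.026 | 0.031 |
| 8/8 | 0.00016 | 0.00033 |

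**How often an occurrences gate is met when all 8 are affected** (one record per dose, independent doses, conditional on each volunteer reacting at least once). At per-dose risks of 0.3, 0.5 and 0.7, the probability of at least 10 occurrences is 0.82, 0.99 and >0.99 over three doses, and 0.43, 0.81 and 0.98 over two.

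**Effect on power.** Let the affected numbers be Bin(8, p1) in one vaccine group, Bin(8, p0) in a comparison group of 8, and Bin(30, p0) in the other 30 volunteers. Ungated power is the probability that Fisher p ≤ 0.05 for the two groups of 8. Gated power also requires at least 10 affected volunteers, or at least 10 occurrences, in the whole trial. For occurrences, the risk is taken as equal and independent over three doses: per-dose risk = 1 − (1 − p)^(1/3), which for p = 0.90, 0.70 and 0.75 is 0.54, 0.33 and 0.37.

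| p1 v p0 (assumed) | Ungated | Gate: 10 volunteers | Gate: 10 occurrences | Gate: 5 volunteers |
|---|---|---|---|---|
| 0.90 v 0.05 | 97% | 37% | 95% | 97% |
| 0.70 v 0.05 | 70% | 12% | 46% | 70% |
| 0.75 v 0 | 89% | 0% | 39% | 89% |

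A gate of 5 volunteers costs nothing here, because no 8 v 8 Fisher comparison reaches 0.05 with fewer than 5 affected.

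**Behaviour of the planned model.** At 8/8 v 0/6 the groups separate completely. An ordinary logistic fit gives a Wald p of 0.998 (standard error about 15,000), although the likelihood-ratio chi-square is 19.1. Lowering the gate alone would therefore not rescue the test if Wald p-values are used.

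**The case against.** A reader might infer that a reaction confined to one group is never tested, even if everyone in the group is affected. The document does not support that in general. The sentence before the gate counts events, and presence or absence per volunteer enters only at the regression step, so counting occurrences is at least as natural a reading. With three doses a group of 8 can then pass 10, and a strong recurring reaction usually would. The claim holds outright only if the unit is volunteers.

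A reader might also infer that four affected volunteers can never give a significant result, so that 5 is a natural limit. That is wrong. Four of 6 in group F against 0/8 gives p = 0.015. In a six-group logistic model on all 46, four affected in one vaccine group and none elsewhere gives a likelihood-ratio chi-square of 16.1 on 5 degrees of freedom, p = 0.007 by the large-sample approximation. The protocol plans a regression for dose and vaccine effects, not pairwise Fisher tests, and that regression may pool groups. The Fisher power figures are therefore illustrative.

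Three further points limit the consequence. Every adverse event is listed and tabulated whatever its count, and 8/8 against 0/6 would be plain in a table. Section 9.4 has safety triggers that do not depend on the gate. Section 10.5 disclaims power for differences between regimens. A minimum count before regression is also a sensible guard against sparse data.

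These points reduce the weight of the issue but do not remove it. The Section 9.4 triggers cover related serious reactions, anaphylaxis and repeated severe events, so mild or moderate reactions in all 8 of a group would not activate them. Limited power explains non-significant results; it does not explain a rule that can skip a comparison with p = 0.00016. Sparse data are better handled by the choice of test than by a gate above the group size.

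**Conclusion.** The concern holds in a limited form. The gate has no unit and exceeds every group size. Counting volunteers, it excludes every one-group reaction. Counting occurrences, it excludes those seen about once per volunteer and makes eligibility depend on repeats that the analysis then discards.

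The size depends on the reading and on the assumed proportions: from almost no loss (97% to 95%, occurrences, 0.90 v 0.05) to complete loss (89% to 0%, volunteers, 0.75 v 0). The occurrences figures assume equal, independent risk over three doses; clustering of repeats within volunteers or a stop after two doses would change them. What is lost is the planned test, not all sight of the reaction. The change is worth making because safety of each formulation is the primary objective and the remedy is small.

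**What to change.** In Section 10.6 and the Synopsis, replace the '10 or more' condition with wording to this effect:

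> Effects of dose and vaccine will be tested for injection-site pain, redness and swelling whatever their count, and for every other event type reported by at least 5 volunteers in the trial, each volunteer counted once. Tests will use an exact method (Fisher or exact logistic regression) or Firth-penalised logistic regression, and are exploratory.

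Five is the smallest one-group excess in a vaccine group that reaches two-sided 0.05 against 0/8 or 0/6. It is a workable choice, not a strict limit: an excess of 4/6 in group F would fall below it. Another threshold attainable within a group of 8 would also serve if the unit is stated. The exact or penalised method is needed together with the lower threshold, because ordinary Wald logistic regression fails under separation.

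The cost is a rewritten condition and method in two places and a few more exploratory p-values. No new data are needed.

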## 6.3 Treatment allocation and randomization

Randomization will be computer generated. The investigator will receive envelopes with numbers (1 to 46) corresponding to the sequence of assignment to the study. In the envelope the assignment to the study group will be determined.

The 18 volunteers recruited in October will first be stratified into males and females and then randomized in blocks of 9 (1 block = females, 1 block = males) into 3 groups: Group A (n = 8) will be vaccinated with 10 µg PEV 301, Group B (n = 8) will be vaccinated with 10µg PEV 302, and 2 volunteers will receive virosomes alone (Group F). If it is not possible to have an equal sex distribution, the blocks can be filled with participants of either sex.

5 weeks later again 18 volunteers have to be recruited, they first will be stratified into males and females and then randomized into 3 groups: group C (n = 8) will be vaccinated with 50 µg PEV 301, group D (n = 8) with 50 µg PEV 302, and 2 volunteers will receive virosomes alone (Group F).

5 weeks after the 2nd vaccination of groups C and D 10 volunteers will be randomized in blocks of 5 to either group E (n = 8) receiving the combination of 50 µg PEV 301 plus 50 µg PEV 302 or group F (n = 2) receiving virosomes alone.

| Time          | N  | Dose       | PEV 301 | PEV 302 | PEV 301+302 | virosomes |
|---------------|----|------------|---------|---------|-------------|-----------|
| November 2003 | 18 | 10 µg      | 8       | 8       |             | 2         |
| December 2003 | 18 | 50 µg      | 8       | 8       |             | 2         |
| March 2004    | 10 | 50 + 50 µg |         |         | 8           | 2         |

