### 8.1 Definitions

#### Adverse event:

An adverse event is any untoward medical occurrence in a patient or clinical trial subject administered a medicinal product and which does not necessarily have to have a causal relationship with this treatment.

This includes any noxious, pathological or unintended change in anatomical, physiological or metabolic functions as indicated by physical signs, symptoms and/or laboratory detected changes occurring in any phase of the clinical study whether associated with the study vaccine, active comparator or placebo and whether or not considered vaccination related. This includes an exacerbation of pre-existing conditions or events, intercurrent illnesses, or vaccine or drug interaction. Anticipated day-to-day fluctuations of pre-existing conditions that do not represent a clinically significant exacerbation need not be considered adverse events. Discrete episodes of chronic conditions occurring during a study period should be reported as adverse events in order to assess changes in frequency or severity.

Adverse events should be documented in terms of signs and symptoms observed by the investigator or reported by the subject at each study visit. A medical diagnosis should be added.

Pre-existing conditions or signs and/or symptoms (including any which are not recognized at study entry but are recognized during the study period) present in a subject prior to the start of the study should be recorded in the medical history part of the subject's CRF.

Adverse events, which occur after informed consent is obtained, but prior to vaccination, will be documented in the medical history part of the subject's CRF.

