## 8.2 Surveillance period for occurrence of adverse events

All adverse events occurring within one month (minimum 30 days) following administration of each dose of vaccine/ placebo must be recorded on the Adverse Event Form in the subject's CRF, irrespective of severity or whether or not they are considered vaccination-related.

Additionally, all serious adverse events brought to the attention of the investigator during the period starting from the day of performance of the first study procedure for each subject and ending not earlier than six months (minimum 180 days) following administration of the last dose of study vaccine for that subject must be recorded. See 8.8 for instructions for recording and reporting of serious adverse events.

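### Section 10.6 tests dose and group effects on adverse events across cohorts never randomised against each other; season could create or mask a combination (E v C/D) effect

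*Protocol*

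**What the plan says.** Protocol 10.6 (Safety data) begins descriptively: "Descriptive statistics will be used to analyze adverse events (AEs) including intercurrent illnesses". It then adds inference: "With frequently occurring (10 or more) event types, effects of dose and vaccine will be tested by" a model fitted to a yes/no outcome for each volunteer. The synopsis repeats the same plan and describes the model as "using logistic regression models to test for differences between groups". The factors named are dose, vaccine and group. No cohort or calendar factor is mentioned.

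Allocation (6.3) takes place in three separate steps. The first reads "The 18 volunteers recruited in October will first be stratified into males and females and then randomized in blocks of 9" and yields A, B and two F. Five weeks later a second set of 18 is randomised to C, D and two F. In March 2004 ten volunteers are randomised to E or F. On the control group, section 3 says "Group F will be distributed and serve as a control in all groups receiving the active product".

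Intercurrent illness is part of the adverse event definition in 8.1: "This includes an exacerbation of pre-existing conditions or events, intercurrent illnesses, or vaccine or drug interaction". Section 8.2 sets the collection period: "All adverse events occurring within one month (minimum 30 days) following administration of each dose of vaccine/ placebo must be recorded", whether or not the event is thought to be vaccine-related. Occurrence of adverse events is listed first among the primary tests (10.2).

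**The concern.** No volunteer could have been randomised between 10 and 50 µg, or between the combination and a single 50 µg component. A regression that reports these as effects of dose or group attributes to the vaccine whatever else differs between cohorts, including recruitment and calendar time.

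Calendar time matters because illness from any cause is counted for a month after each dose, and the cohorts were dosed in different seasons. The risk runs both ways. A lower illness rate in E could look like good tolerability. A true excess in E could be offset because C and D were observed in winter. The second is the more serious, since this is the first study of these products in humans (8.3.1) and E is where they are given together.

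**Working it through.** **Inputs from the protocol.** Allocation (6.3) and vaccination weeks (Flow Chart):

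| Cohort | Groups | Dosing weeks | Windows starting Nov–Feb |
|---|---|---|---|
| 1 | A 8, B 8, F 2 | 46/2003, 3/2004, 20/2004 | 2 of 3 |
| 2 | C 8, D 8, F 2 | 51/2003, 8/2004, 25/2004 | 2 of 3 |
| 3 | E 8, F 2 | 13/2004, 22/2004, 39/2004 | 0 of 3 |

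The total reproduces: 18 + 18 + 10 = 46 and 5 × 8 + 6 = 46. No event rate or significance level is stated, so there is no power figure to reproduce.

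**Which contrasts are randomised.** PEV 301 v PEV 302 at one dose (A v B, C v D) and active v F within a cohort are. The contrasts 10 v 50 µg (A+B v C+D) and E v C/D are not. Each coincides exactly with a cohort boundary.

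**Assumptions.** The probability of illness is w in a window starting November to February and s in any other, independently across windows. Tests are two-sided at 5%. There is no vaccine effect unless stated.

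**Ever-ill rates.** A to D: 1 − (1−w)²(1−s). E: 1 − (1−s)³.

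- w = 0.20, s = 0.07: 1 − 0.64 × 0.93 = 0.405 for A to D; 1 − 0.804 = 0.196 for E.
- w = 0.10, s = 0.05: 1 − 0.81 × 0.95 = 0.231; 1 − 0.857 = 0.143.
- w = 0.30, s = 0.10: 1 − 0.49 × 0.90 = 0.559; 1 − 0.729 = 0.271.

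In the middle case the expected number ever ill is 36 × 0.405 + 10 × 0.196 ≈ 16.5 across all illness types, so the threshold of 10 could be met. In the low case it is 36 × 0.231 + 10 × 0.143 ≈ 9.7, about at the threshold.

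**E (8) v C+D (16).** Rejection probability by full enumeration of two binomials, ignoring the threshold:

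| Scenario | E v C+D rates | Likelihood ratio | Fisher |
|---|---|---|---|
| No season effect | 20% v 20% | 0.070 | 0.016 |
| Season only, middle (rates rounded) | 20% v 40% | 0.195 | 0.069 |
| Season only, low | 14% v 23% | 0.099 | 0.008 |
| Season only, high | 27% v 56% | 0.296 | 0.187 |

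**Masking.** Suppose the combination truly doubles the rate from 20% to 40%. Without a season effect (40% v 20%), likelihood-ratio detection is 0.219. If season also lifts C+D to 40% (40% v 40%), it is 0.063, about the test's false-positive rate.

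**Dose.** A+B and C+D have the same number of winter windows, so this model gives both 0.405. The 16 v 16 likelihood-ratio test then rejects in 0.052, which is no seasonal inflation.

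**Would a cohort term repair it?** Cross-cohort contrasts would then be identified only through two controls per cohort. Taking variance as proportional to the sum of 1/n:

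- 10 v 50 µg: (1/16 + 1/2 + 1/16 + 1/2) ÷ (1/16 + 1/16) = 9.0.
- E v C+D: (1/8 + 1/2 + 1/16 + 1/2) ÷ (1/8 + 1/16) = 6.3.
- E v C: (1/8 + 1/2 + 1/8 + 1/2) ÷ (1/8 + 1/8) = 5.0.

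In simulation the adjusted test ran at about 0.07 to 0.12 under the null. The within-cohort test E (8) v F (2) detects 40% v 20% in only 0.044 of trials by likelihood ratio.

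**The case against.** Several counter-arguments carry weight.

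- **The model is only sketched.** A reader might infer that 10.6 pools F across cohorts and rules out a cohort term. It states neither. An SAP could add a term, and section 3 describes F as spread over the cohorts. This stands. It does not remove the problem: 6.3 fixes the confounding, and no later model makes these contrasts randomised.
- **E v C+D is not prescribed for safety.** E against C or D is named only for the immunogenicity Wilcoxon tests. It is one of the group differences the safety wording implies, and is used here as an illustration.
- **A seasonal dose effect.** A reader might infer that season also distorts 10 v 50 µg. The flow chart does not support this: cohorts 1 and 2 start five weeks apart with similar seasonal exposure.
- **The rates and the winter cut-off are assumed.** C/D's second dose (week 8) counts as winter and E's first (week 13) does not, although they are five weeks apart. E's third window runs into October. With a low rate pair, or with Fisher's test, the inflation is small or absent.
- **Limited reach.** Safety rests mainly on listings and frequency tables. Section 10.5 disclaims power for differences between regimens. The triggers for a safety board (9.4) and the interim rule (10.8) do not use this test. Local reactions should be little affected by season, and the phrase on intercurrent illnesses in 10.6 sits in the descriptive sentence; illness reaches the test through the definition in 8.1. All true, but low power does not excuse presenting a confounded contrast as a tested effect.
- **Sequential cohorts are inherent in dose escalation.** Agreed. The point concerns how the comparisons are analysed and labelled, not the design.

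**Conclusion.** The point holds in a limited form. The 10 v 50 µg and E v C/D comparisons of adverse events are fully confounded with cohort, yet the protocol plans to test dose and group effects as though the groups had been randomised together. That follows from the document alone.

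The size of any seasonal distortion does not; it rests on assumed illness rates. In the middle case, season alone raises rejection for E v C+D from 7% to about 20% by likelihood ratio (2% to 7% by Fisher). In the low case it is about 10% (1%). A true doubling in E could be hidden, with detection falling from 22% to 6%, although 22% is already poor. The exposure is confined mainly to non-local events in E v C/D. No material seasonal dose bias is shown, and PEV 301 v PEV 302 at one dose is sound. The wording should be changed before analysis; the design need not be.

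**What to change.** Amend 10.6 and the matching synopsis text:

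1. Test PEV 301 v PEV 302 within cohorts 1 and 2, where it is randomised.
2. Report active v concurrent F by cohort as estimates with exact intervals, not as a powered test.
3. Report 10 v 50 µg and E v C/D adverse event differences as non-randomised descriptive comparisons, with no claim of a tested effect.
4. Tabulate intercurrent illnesses by calendar period, separately from solicited reactions.

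A cohort-adjusted test of dose or combination is not a substitute, given the five- to nine-fold variance increase.

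Cost: analysis wording only, with no new data. The trial gives up a tested dose or combination claim on adverse events, and the within-cohort control contrasts will be very imprecise with two controls each.
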